### Randomization

A balanced 1:1 block (size six) randomization stratified by center will be performed directly after surgery, using Research Manager (RM; version 4.5.0.1), a web-based computer program (Fig. 1). A research nurse who is not involved in the study generates the allocation sequence with RM. Intramedullary hip nail (IMHN), dynamic hip screw (DHS) and cannulated screws are grouped for block randomization, as are total hip arthroplasty (THA) and hemiarthroplasty (HA). The intervention group ‘A’ will receive CFC therapy postoperative; the control group ‘B’ will receive standard care. Due to the nature of the study no blinding can exist as patients, family and physicians notice the use and settings of CFC therapy. Physicians randomize participants with a digital logon to the web-based system or the physician can contact the coordinating investigator and he will randomize the included participant (see Table 1 for criteria).The Informant Questionnaire for the Cognitive Decline in the Elderly (IQ-CODE) questionnaire is administered when the clinician has doubts about the cognitive state that may compromise CFC therapy sessions or study measurements (Table 1). Ideally a MMSE would be used for this purpose, however due frequently perceived pain at the accident and emergency A&E department and consequently administered narcotic analgesics, the hetero anamnestic IQ-CODE is used instead. The coordinating investigator contacts the participating hospitals on a daily basis by telephone or physically to ensure adequate and appropriate enrollment of participants and completeness of data. A list of excluded patients will be drafted.

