### Length of stay

Admission time is measured and expressed in two ways: from arrival time at the A&E department until discharge and from end of surgery to until discharge. The discharge criteria in all participating centers are: NRS-pain score below 5 without need for parenteral analgesics and an Elderly Mobility Scale (EMS) score 14 out of 20 or higher [63, 64]. If this some items were deemed unobtainable EMS scores are completed until transfer to a nursing home is arranged. If family members are able to foresee in certain home care aspects the patient can be discharged to his/her home. The fulfillment of this care by family is noted and corrected for afterwards.

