## Statistics

### Analysis of outcome parameters

All statistical analyses will be computed using the SPSS statistical package (IMB SPSS, Inc., Release 20.0.0.0, 64-bit edition). Statistical analysis will be performed according to the intention-to-treat principle. Baseline characteristics will be described in accordance with CONSORT guidelines [41] using means and standard deviation in case of normal distribution, and medians and interquartile ranges otherwise. Continuous variables will be checked for normality, visually and by using the Shapiro Wilk test. Our primary analysis focuses on the differences in NRS-pain scores between the study groups 24 h postoperative and will be analyzed by use of Student’s T or Mann–Whitney U tests in case of skewed distribution. To assess treatment effect over time, a mixed model analysis for repeated measures will be performed. This model allows missing data and adjustment for serious confounders and interactions. In case of skewed distributions and outliers non-parametric variants will be used (e.g. Mann Whitney U or Friedman tests). Secondary continuous outcome measures (EQ-5D-3L, SF-12, DRS-R-98 and hemoglobin) will be compared by use of Student’s t or Mann Whitney U tests. Ordinal variables will be analyzed using the Mann–Whitney test. Chi-squared tests will be performed in case of categorical variables. In case of important confounding, analysis will be adjusted to correct for these factors (by use of multiple regression analysis, linear or logistic). A *p*-value of < 0.05 will be considered statistically significant.

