### Sample size calculation

Sample size calculation is based on the primary outcome measure, NRS-pain at 24 h postoperatively. Subsequently, a mean NRS-pain score for postoperative day one was drawn from the Spaarne Gasthuis electronic patient dossier digital databanks and a standard deviation of 2.2 was calculated for pooled internal fixation and (hemi) arthroplasty for cervical and peritrochanteric fractures. The minimal clinical relevant difference for NRS-pain is 1.3 out of 10 [53]. The alpha was set at 5 % with a power of 90 % due to anticipated heterogeneity in regard to operating techniques, general care protocols but predominantly in regard to pain protocols between the participating centers (Table 2). An expected NRS failure rate of 10 % is anticipated together with expected missing data a drop out of 22.3 % is computed. The total number of included patients will be 160.

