Currently three of the four participating hospitals have a geriatric trauma unit, in one of the hospitals with a geriatric trauma unit the care of the surgical geriatric patient is transmitted to the geriatrician in full except for wound assessments and related care. At this ward all patients receive prophylactic haloperidol 1 mg daily, and more if needed. At the hospital without a geriatric trauma unit a geriatrician is not readily available and unable to attend the clinic on a daily basis. Confounding of secondary outcomes as delirium, psychotropic medication and functional outcome can therefore not be ruled out.

When compared to the preoperative values, hemoglobin levels in collected blood samples at postoperative day one are usually much lower than one would expect from the observed blood loss during surgery. This gap called ‘the hidden blood loss’ is thought to arise from, among others gastro-intestinal bleeding [22, 79]. The amount of (hidden) blood loss is more severe when oral anticoagulants or thrombocyte aggregation inhibitors compromise a patient’s hemostasis and this loss may continue throughout the early postoperative period. Hemoglobin measured at postoperative day one is most likely, as opposed to the preoperative values, significantly diluted, thereby underestimating the actual hemoglobin concentration. Combined with the possibility of hidden blood loss throughout the hospital stay, care has to be taken when comparing the value of postoperative day one to day three.

The functional outcome assessment of patients who are not allowed to bear weight at the time of discharge is postponed to the outpatient clinic. At this visit they are allowed to bear weight for the first time in weeks. Testing directly after weight bearing for the first time can introduce confounding.

Finally, care has to be taken to interpret the allocation to rehabilitation facilities. For instance patients who have sufficient family members who can help out at home are more likely to be discharged home with or without homecare rather than be assigned to a rehabilitation clinic or nursing home with rehabilitation facilities.

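### Length of stay has no pre-specified baseline adjustment: covariates enter only on undefined confounding, so available precision is left unused

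*Protocol article*

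**What the plan says.** The Aim section ends its hypotheses with shorter length of stay, as the consequence of better functional recovery. The Length of stay section defines the outcome twice: "Admission time is measured and expressed in two ways: from arrival time at the A&E department until discharge", and also from the end of surgery. Discharge requires an NRS-pain score below 5 without parenteral analgesics, together with "an Elderly Mobility Scale (EMS) score 14 out of 20 or higher". There is a nursing-home route when mobility items cannot be attained, and discharge home is possible where family can provide care. Family care is recorded and corrected for afterwards. That is the only correction tied to length of stay.

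Under Analysis of outcome parameters, the relevant sentence begins "Secondary continuous outcome measures (EQ-5D-3L, SF-12, DRS-R-98 and hemoglobin) will be compared by use of" and goes on to Student's t or Mann-Whitney tests. Length of stay is not in its list. Ordinal and categorical outcomes get Mann-Whitney and chi-squared tests. Adjustment by multiple regression follows only in case of important confounding, with no criterion and no covariates named.

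The Randomization section states: "A balanced 1:1 block (size six) randomization stratified by center will be performed directly after surgery". Surgery types are grouped into internal fixation and arthroplasty for the blocks, and the Discussion confirms stratification by type of surgery. NMS and Katz-ADL are recorded on admission (Admission section, Table 4). On differences between hospitals the Discussion says: "Currently three of the four participating hospitals have a geriatric trauma unit".

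**The concern.** In a randomised trial, any baseline difference between arms is due to chance. The reason to adjust is that a factor predicts the outcome, and that can be decided in advance. A rule triggered by confounding seen in the data has two drawbacks. It leaves the model open until results are visible, in an open-label trial. It also brings in covariates because they happen to be imbalanced, not because they are prognostic.

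For length of stay the candidate factors are known now. Centre and surgery group were balanced by design, and an analysis that ignores them does not use that balance. Pre-fracture function plausibly bears on the mobility part of the discharge rule. If these factors are prognostic, leaving them out keeps their variation in the error term, and a real shortening of stay is more likely to be missed. A Mann-Whitney p-value would also give no estimate in days or per cent.

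The family-care correction does not fill the gap. It uses something that acts at discharge, after randomisation.

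**Working it through.** **1. The plan's own figure.** The Sample size calculation covers NRS-pain at 24 h only. Its inputs are "The alpha was set at 5 % with a power of 90" per cent, "a standard deviation of 2.2 was calculated for pooled internal fixation and (hemi) arthroplasty" and "The minimal clinical relevant difference for NRS-pain is 1.3 out of 10", with 22.3% drop-out.

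- Normal approximation, two-sided: n per arm = 2 × 2.2² × (1.960 + 1.282)² / 1.3² = 60.2, so 61. Then 122 / (1 − 0.223) = 157.0, so 158.
- Exact t-test: 62 per arm. Then 124 / 0.777 = 159.6, so 160.

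The stated total of 160 reproduces. No power is stated for length of stay.

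**2. Inputs for length of stay.** From the document: 160 patients, so 80 per arm, and a difference of 1.4 days, cited in the Background from a study of cryotherapy after hip arthroplasty. Assumed, because the document gives neither: mean stay 9 days, SD of log stay 0.6, and R², the share of variance explained by centre, surgery group, NMS and Katz-ADL.

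**3. Formula.** Effect on the log scale = −ln(1 − 1.4/9) = 0.169. Standard error = 0.6 × √(1 − R²) × √(2/80). Power = Φ(effect/SE − 1.96).

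| R² | SE | effect/SE | Power | Unadjusted N of equal precision, 160/(1 − R²) |
|---|---|---|---|---|
| 0 | 0.0949 | 1.78 | 43% | 160 |
| 0.05 | 0.0925 | 1.83 | 45% | 168 |
| 0.10 | 0.0900 | 1.88 | 47% | 178 |
| 0.20 | 0.0849 | 1.99 | 51% | 200 |
| 0.30 | 0.0794 | 2.13 | 57% | 229 |
| 0.40 | 0.0735 | 2.30 | 63% | 267 |

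**4. Range.** With mean stay 7 to 12 days and log SD 0.5 to 0.7, unadjusted power runs from 20% to 81%, and R² = 0.30 adds about 7 to 15 points. On the raw scale, with assumed SDs of 3, 4, 5 and 6 days, power for 1.4 days is 84%, 60%, 43% and 31% unadjusted, and 91%, 70%, 51% and 38% at R² = 0.20.

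**5. Validity.** A simulation of 4,000 trials per setting used blocks of six within five centres and two surgery groups. Centre explained 5–10% of the variance and one baseline covariate 10–20%. The effect was 0.443 SD, which gives 80% unadjusted power.

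- Unadjusted t-test: type I error 4.2–4.8%, power 80–81%.
- Adjusted for the strata: power 82–84%.
- Strata plus the covariate: power 85–92%.

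Ignoring the strata makes the test slightly conservative, not invalid. Most of the gain comes from the baseline covariate.

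**The case against.** The strongest objection is that the quoted sentence does not cover length of stay, and that an article may leave the model for a secondary outcome to the analysis plan. The first part is correct. A reader might infer that the protocol prescribes an unadjusted t or Mann-Whitney test for length of stay, but it does not: the outcome has no named test, and the unadjusted default follows only from the rest of the section. The second part also stands as far as it goes, since a missing model would not be a finding in itself. What remains is the adjustment rule. It is stated, is not limited to particular outcomes, and makes baseline covariates depend on the data.

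Other tempting readings also fail:

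- **That discharge is purely a mobility threshold.** It also has a pain and parenteral-analgesic condition, a nursing-home route and a role for family support. This weakens the link from NMS and Katz-ADL to length of stay without removing it.
- **That length of stay is strongly determined by these factors.** No figure in the document says so. NMS stratification is mentioned in the Timed Up and Go section, and the Discussion links geriatric-unit differences to delirium, psychotropic medication and functional outcome, not to length of stay.
- **That the plan makes no correction at all for length of stay.** It plans one for family care.
- **That the planned comparison is biased or the sample size wrong.** Neither is shown. The trial is powered for pain only.

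The 1.4-day effect comes from a different population, and at R² of 0.05–0.10 the gain is only about 2 to 4 points.

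**Conclusion.** The point holds as one of efficiency and pre-specification, not validity. By default no baseline factor enters the length-of-stay comparison, and the only route in is an undefined, data-dependent trigger. In the central case the loss is about 2 to 4 percentage points of power at R² of 0.05–0.10, 8 at 0.20, 14 at 0.30 and 20 at 0.40. These sizes depend on an assumed mean, log SD and R², and on an effect borrowed from hip arthroplasty. The direction requires only that the factors be prognostic. Because the trial was not sized for length of stay, precision from data already collected is worth having.

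**What to change.** For length of stay, replace the confounding-triggered rule with one pre-specified analysis: a linear model on log hours from end of surgery to discharge, with arm, centre and surgery group (as used in the randomisation), NMS and Katz-ADL. Report the ratio of geometric means with its 95% CI. If a rank test is preferred, use the van Elteren test stratified by centre and surgery group. Keep the definition from A&E arrival and the family-care correction as sensitivity analyses. Report in-hospital deaths separately, since a model of time to discharge does not by itself account for them.

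The cost is a change of wording and slightly more analysis work. All covariates are already collected before randomisation, and the protocol already names linear regression.

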### Sample size calculation

Sample size calculation is based on the primary outcome measure, NRS-pain at 24 h postoperatively. Subsequently, a mean NRS-pain score for postoperative day one was drawn from the Spaarne Gasthuis electronic patient dossier digital databanks and a standard deviation of 2.2 was calculated for pooled internal fixation and (hemi) arthroplasty for cervical and peritrochanteric fractures. The minimal clinical relevant difference for NRS-pain is 1.3 out of 10 [53]. The alpha was set at 5 % with a power of 90 % due to anticipated heterogeneity in regard to operating techniques, general care protocols but predominantly in regard to pain protocols between the participating centers (Table 2). An expected NRS failure rate of 10 % is anticipated together with expected missing data a drop out of 22.3 % is computed. The total number of included patients will be 160.

## Dissemination policy

The trial outcome will be published as an international peer-reviewed article. Any modifications to the protocol which may impact on the conduct of the study, potential benefit of the patient or may affect patient safety, including changes of study objectives, study design, patient population, sample sizes, study procedures, or significant administrative aspects will require a formal amendment to the protocol. Such amendment will be agreed upon by the REC/IRB and will be reported to www.trialregister.nl and to this journal.

## Discussion

This multicenter study will evaluate the efficacy of intermittent application of continuous-flow cryocompression therapy administered in the first 72 postoperative hours after hip fracture surgery. Due to the multicenter design of the study the results can easily be translated to the general care of hip fracture patients. Conversely, some inequality in local hospital pain protocols is present but conversion through accepted algorithms [59, 60] make comparison feasible. Spinal anesthetized patients could have advantages over the general anesthesia group in the acute hours post-surgery in regard to pain scores and analgesic use since the effect of the latter ends immediately after surgery in contrast to the former that takes a few hours to wear off completely.

The varying types of fractures have different characteristics and demand a different surgical approach. Peritrochanteric fractures quite often have more extensive bony trauma and less soft-tissue trauma, and after surgical stabilization with a DHS or IMHN fracture micro-motion leads to prolonged and greater dynamic pain [6]. Conversely, in (hemi) arthroplasty the fracture-site is removed completely at the expense of increased (surgical-induced) soft-tissue trauma. Hence the efficacy of CFC therapy is likely to vary in patients with varying extent of soft-tissue trauma. Therefore stratification is implemented according to type of surgery that divides patients with greater surgical trauma ((hemi) arthroplasty) and lesser surgical trauma (cannulated screws, DHS, IMHN).

By nature, delirium is known to fluctuate over the day and a single DRS-R-98 measurement might not reach sufficient sensitivity for diagnosis. However with longitudinal follow-up of three times daily DOS-scores this problem is overcome for the most part. Delirium severity is assessed with more information gathered from family and personnel, over the past 24 h thereby making assessment adequate.

Currently three of the four participating hospitals have a geriatric trauma unit, in one of the hospitals with a geriatric trauma unit the care of the surgical geriatric patient is transmitted to the geriatrician in full except for wound assessments and related care. At this ward all patients receive prophylactic haloperidol 1 mg daily, and more if needed. At the hospital without a geriatric trauma unit a geriatrician is not readily available and unable to attend the clinic on a daily basis. Confounding of secondary outcomes as delirium, psychotropic medication and functional outcome can therefore not be ruled out.

When compared to the preoperative values, hemoglobin levels in collected blood samples at postoperative day one are usually much lower than one would expect from the observed blood loss during surgery. This gap called ‘the hidden blood loss’ is thought to arise from, among others gastro-intestinal bleeding [22, 79]. The amount of (hidden) blood loss is more severe when oral anticoagulants or thrombocyte aggregation inhibitors compromise a patient’s hemostasis and this loss may continue throughout the early postoperative period. Hemoglobin measured at postoperative day one is most likely, as opposed to the preoperative values, significantly diluted, thereby underestimating the actual hemoglobin concentration. Combined with the possibility of hidden blood loss throughout the hospital stay, care has to be taken when comparing the value of postoperative day one to day three.

The functional outcome assessment of patients who are not allowed to bear weight at the time of discharge is postponed to the outpatient clinic. At this visit they are allowed to bear weight for the first time in weeks. Testing directly after weight bearing for the first time can introduce confounding.

Finally, care has to be taken to interpret the allocation to rehabilitation facilities. For instance patients who have sufficient family members who can help out at home are more likely to be discharged home with or without homecare rather than be assigned to a rehabilitation clinic or nursing home with rehabilitation facilities.

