### Standard care

On arrival at the accident and emergency (A&E) department patients receive acetaminophen intravenously, diclofenac (if not contraindicated) and morphine subcutaneously or fentanyl intravenously until numerical rating scale (NRS)-pain scores have dropped below 4. Upon admission the local protocol is started (Table 2). At all centers the 'as needed' medication is administered when the NRS-pain score is 4 or higher and no excessive (opioid-induced) sedation is present. Patients who are deemed able are given intravenous patient controlled analgesia (PCA) pumps with morphine (Table 2). In patients older than 70 years the bolus setting is reduced by 50 %. Preferably patients are operated on using spinal anesthesia. In order to put the patient in an upright position for spinal anesthesia administration femoral blocking with short-acting analgesics can be used. All centers use bupivacaine 0.5 % between 2.0 and 3.0 ml administered at the lumbar level. Additional (long acting) analgesics administered during surgery are noted. The participating centers adhere to the Dutch national guidelines for surgical technique for the various fracture types [43]. Postoperatively, on the day of surgery or the first postoperative day physical therapy is commenced once or twice daily. Physical therapy sessions are usually 30 min long. In the period in which the focus of this study lies physical therapy focuses on strengthening of quadriceps and gluteal musculature, walking and making transfers.

**Table 1 Tab1:** Criteria for participants in the trial

Inclusion criteria	Exclusion criteria
* Intra or extracapsular proximal femur fracture	* Fractures at multiple foci
	* Open fracture/wounds^a^
* Aged 18 years and over	* Acetabular fracture
* Informed consent or proxy consent	* (Suspicion of) concomitant malignancy
	* BMI > 40
	* Unwilling to give proxy consent
	* Preoperative osteosynthesis materials in situ in the ipsilateral leg above knee level
	* Morphine allergy or dependence
	* ASA ≥ 4
	* Cryoglobulinemia
	* M. Raynaud
	* Central neuromuscular disorder
	* Absent ADP/ATP pulsations in the injured extremity
	* Active deep vein thrombosis
	* Suspected pulmonary embolism
	* Patient delay > 24 h
	* NYHA-class ≥ 3
	* IQ-CODE score ≥ 4.6*
	* Long-acting femoral blocks
	* Use of LIA
	* Postoperative HD-instability

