^a^Open wounds unable to close per primam, * The IQ-CODE is only administered if the clinician has doubts about the cognitive status of the intented participant

*BMI* body mass index, *ASA* American Society of Anesthesiologists, *ADP* dorsal pedal artery, *ATP* posterior tibial artery, *NYHA* New York Heart Association, *IQ-CODE* Informant Questionnaire for the Cognitive Decline in the Elderly, *LIA* local infiltration anesthesia, *HD* hemodynamic

**Table 2 Tab2:** Hospital protocols

		Analgesic protocol				
Hospital	Thrombosis prophylaxis	Standard		As needed		
Spaarne Gasthuis, Hoofddorp	Fraxiparine 2850 IU 1x^a^	Acetaminophen 1000 mg 4x	Diclofenac 50 mg 3x^b^	PCA-iv morphine	*or*	Morphine 10 mg 6x sc^c^ *or* Oramorph 10 mg 6x^c^
				*If considered able*		
Noordwest Ziekenhuisgroep	Fraxiparine 2850 IU 1x^a^	Acetaminophen 1000 mg 4x	Diclofenac 50 mg 3x^b^	PCA-iv morphine	*or*	Morphine 10 mg 6x sc^c^ *or* Oxycodone 10 mg 6x^c^
				*If considered able*		
VU University medical center	Fraxiparine 2850 IU 1x^a^	Acetaminophen 1000 mg 4x	Diclofenac 50 mg 3x^b^	Morphine 10 mg 6x sc^c^	*or*	Oxycodone 10 mg 6x^c^
Spaarne Gasthuis, Haarlem	Fraxiparine 2850 IU 1x^a^	Acetaminophen 1000 mg 4x	Diclofenac 50 mg 3x *or* 75 mg iv 2x^b^	Morphine 10 mg 6x sc^c^	*or*	Oxycodone 10 mg 6x^c^
Amstelland Hospital	Enoxaparine 40 mg 1x	Acetaminophen 1000 mg 3x	Diclofenac 75 mg im/iv 2x^b^	PCA-iv morphine	*or*	Piritramide 10 mg 6x sc^c^ *or* Tramadol 50 mg 3x
				*If considered able*		

Reported dosages are dosages given in 24 h

*im* intramuscular, *iv* intravenous, *sc* subcutaneous, *PCA* patient controlled analgesia

^a^Dosage is doubled in patients weighing > 80 kg

^b^If no contraindications exist. ^c^: Dosage is reduced by 50 % in patients aged ≥ 70 years

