### Analgesic use

All postoperative oral and parenteral administered narcotic analgesics will be converted and added up using accepted algorithms [59, 60] and compared after the last treatment day, at discharge and at the outpatient clinic. Total milligrams of acetaminophen and non-steroidal anti-inflammatory drugs (NSAID’s) are reported in the same fashion. At the outpatient visit patients will be asked about their current pain medication use.

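### Converting opioids to one unit does not equalise the local pain protocols; naming centre and age in advance in the morphine comparison would avoid a small to moderate loss of precision

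*Protocol article*

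**What the plan says.** All references are to the Protocol article.

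- **Outcome.** Analgesic use says that postoperative "narcotic analgesics will be converted and added up using accepted algorithms [59, 60] and compared after the last treatment day", and again at discharge and at the outpatient visit. Aim makes lower morphine consumption part of the first hypothesis.
- **Claim.** The Discussion says that "some inequality in local hospital pain protocols is present but conversion through accepted algorithms [59, 60] make comparison feasible".
- **Site differences.** In Table 2 (Standard care), PCA morphine is an as-needed option at Hoofddorp, Noordwest and Amstelland, for patients considered able, and is not listed at VU or Haarlem. Amstelland also lists acetaminophen three rather than four times daily, and piritramide or tramadol.
- **Age differences.** Footnote c of Table 2, attached to most as-needed opioids but not to tramadol, reads "Dosage is reduced by 50 % in patients aged ≥ 70 years". For PCA, the text of Standard care reads "In patients older than 70 years the bolus setting is reduced by 50" per cent.
- **Allocation.** "A balanced 1:1 block (size six) randomization stratified by center will be performed directly after surgery". Surgery types are grouped for the blocks, and the Discussion treats surgery type as a stratum. Age is not one.
- **Analysis.** "Secondary continuous outcome measures (EQ-5D-3L, SF-12, DRS-R-98 and hemoglobin) will be compared by use of Student’s t or Mann Whitney U tests". Regression adjustment follows only where important confounding is present; no covariate or threshold is named.

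**The concern.** Conversion answers one question: how many morphine milligrams a dose of another opioid is worth. It does not answer how much a patient could receive under the local rules. Those rules differ by site and by age group, so the converted total can be expected to vary with both, whatever the arm. The Discussion presents conversion as what makes the comparison workable.

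The analysis section does not fill the gap. A rule that adjusts only when confounding appears is aimed at imbalance between arms. Centre is balanced by design, so it will seldom look like a confounder. It still adds variance to the outcome, and an unadjusted test leaves that variance in the standard error.

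Morphine use also matters beyond its own test. Standard care gives as-needed analgesia when the pain score is 4 or higher, so the pain comparison has to be read alongside opioid use. An imprecise morphine result makes that reading harder.

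**Working it through.** **1. The plan's own figure.** The only sample size stated is for pain at 24 h: difference 1.3, SD 2.2, alpha 5%, power 90%, dropout 22.3%, total 160.

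- Normal approximation, two-sided: n per arm = 2 × (1.960 + 1.282)² × (2.2/1.3)² = 60.2, so 61; total 122; 122/0.777 = 157.0, rounded up to 158.
- t-based: 61.2, so 62 per arm; 124/0.777 = 159.6, so 160.

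The figure reproduces, and nothing below touches it. No SD, effect or power is given for morphine use.

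**2. Variance due to age and site (assumed inputs).** On the log scale, let p be the share aged 70 or over, q the share of patients at PCA sites, f the ratio of use at PCA to non-PCA sites, and s the residual SD. If halving the dose carries through fully to consumption:

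- V = p(1−p)(ln 2)² + q(1−q)(ln f)²
- share explained R² = V/(V + s²)
- sample-size inflation without adjustment = 1/(1 − R²)

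Mid case p = 0.8, q = 0.6, f = 1.5, s = 0.8:

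- V = 0.16 × 0.480 + 0.24 × 0.164 = 0.077 + 0.039 = 0.116
- R² = 0.116/(0.116 + 0.640) = 0.154; inflation 1.18
- effect with 80% power after adjustment at 62 per arm: 0.8 × 2.802 × √(2/62) = 0.403 on the log scale, about a one-third reduction
- unadjusted: 0.403/(√0.756 × √(2/62)) − 1.960 = 0.62, so power is 73%

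Other cases, each set to 80% power when adjusted (q = 0.6, 62 per arm):

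| p | f | s | R² | Unadjusted power | Inflation |
|---|---|---|---|---|---|
| 0.9 | 1.0 | 1.1 | 0.035 | 79% | 1.04 |
| 0.9 | 1.5 | 0.8 | 0.114 | 75% | 1.13 |
| 0.8 | 1.5 | 0.8 | 0.154 | 73% | 1.18 |
| 0.8 | 2.0 | 0.8 | 0.231 | 69% | 1.30 |
| 0.7 | 2.0 | 0.5 | 0.464 | 54% | 1.86 |

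**3. Simulation with blocks of six within centre (3000 trials, 124 patients).** Mid case: Mann-Whitney 72%, log-scale t-test 74%, model with centre and age 79%. So about 2 of the 7 points come from the choice of test and about 5 from the covariates. With no true effect, the unadjusted tests rejected in 2.1% to 4.7% of trials across five settings, lowest where site and age effects were strongest.

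**4. At 160 patients, true 30% reduction.**

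- Strong inputs (25% under 70 using twice as much, PCA ratio 1.0 to 2.0). Mann-Whitney against adjusted model, residual log-SD 0.7: 84.2/90.8, 80.7/90.3 and 76.4/89.5%; log-SD 0.9: 64.3/70.4, 62.4/70.2 and 59.2/70.6%. Gains are 6 to 13 points.
- Mild inputs (10 to 20% under 70 using 1.4 times as much, PCA ratio 1.0 to 1.25). Mann-Whitney to adjusted model gains about 1 to 4 points (for example 86.5 to 89.6%); log-scale t-test to adjusted model gains about 0 to 2 (88.8 to 89.6%).

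**5. Bias.** Centre is balanced by stratification. For age, the 95% limit of chance imbalance at 62 per arm and p = 0.8 is 1.96 × √(2 × 0.8 × 0.2/62) = 0.141. Times ln 2 this is 0.098, a factor of 1.10 in either direction. That is random error, not a systematic shift.

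**The case against.** Several stronger readings are tempting, and the documents do not support them.

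- **A reader might infer that morphine use will be analysed with no adjustment at all.** The article does not fix that. Analgesic use is missing from the bracketed list of secondary continuous outcomes, and regression is foreseen for important confounding. Age is not a stratum, so a chance age imbalance is a case that clause could cover. Covariates for a secondary outcome are also often left to the analysis plan. What stands is narrower: no other method for a continuous secondary outcome is stated, and the stated trigger is unsuited to a factor that is balanced by design.
- **A reader might infer that the dose rules hide or dilute a true sparing effect.** They do not bias the comparison; randomisation takes care of that. The loss is in precision.
- **A reader might infer that the Discussion declares the problem solved.** It says only that comparison becomes feasible, and it concedes inequality between protocols in the same sentence. The reasoning is still incomplete, because a common unit does not address the inequality conceded.
- **The size rests on assumptions.** Halving a dose or bolus need not halve consumption, since as-needed doses can be repeated and PCA is patient-controlled. PCA goes only to patients considered able, which weakens any site effect. The Conclusion expects patients generally aged 70 and over, which shrinks the age component. Setting Mann-Whitney against a log-linear model on log-normal data also credits part of the gain to the covariates wrongly. All of this stands, and it is why the low end of the range must be shown.

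**Conclusion.** The point holds as a minor one on a secondary outcome. Unit conversion does not make unequal prescribing rules comparable, and the plan names no centre or age term for the outcome on which those rules act most directly.

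The consequence is a wider interval for both factors and, because allocation is stratified by centre, a conservative test when centre is ignored. It cannot be sized from the documents. Under the assumed inputs it runs from about 1 to 13 power points at 160 patients. The upper end needs a full two-fold age effect, a two-fold PCA-site effect and a small residual spread. None of the simulated settings showed a loss of power from adjusting. The primary pain analysis and the total of 160 are unaffected.

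**What to change.** 1. Pre-specify the 72 h morphine-equivalent comparison with arm, centre, surgery group and age in the model, on a scale suited to skewed data. One choice is a linear model on the log total, reported as a ratio of geometric means with its confidence interval and with the handling of zero totals fixed beforehand. If many patients may take no opioid, a rank test stratified by centre (van Elteren) avoids the added constant. Crossing centre with age group could leave very small strata under 70.
2. Enter age as a continuous variable, so that the model needs no cut-off.
3. Reword the Discussion sentence: conversion gives a common unit, and the centre and age terms handle differences between local protocols.
4. Reconcile the age limits. The PCA rule in the text of Standard care applies above 70, and footnote c of Table 2 applies from 70.

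The cost is wording only: centre is already a stratum and demographics are recorded at baseline. The price in the analysis is a few degrees of freedom, an estimate that is not in milligrams if a log scale is used, a rule for zeros, and a continuous age term that follows a step near 70 less closely than a category would.
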